### Follow-up of adverse events

Adverse events likely to be related to the study drug, whether serious or not, which persist at the end of the trial will be followed up by the investigator until their resolution or stabilisation, or until causality is determined to be unrelated to trial interventions. All AEs will be managed as per Kenyan national clinical guidelines.

Moreover, any serious adverse event likely to be related to unithiol and occurring after trial termination should be reported by the investigator according to the procedure described below.

Outcome of any non-serious adverse event occurring within 6 months of the last dose of unithiol (i.e., unsolicited adverse event) or any SAE reported during the entire study will be assessed as:

•      Recovered/resolved

•      Not recovered/not resolved

•      Recovering/resolving

•      Recovered with sequelae/resolved with sequelae

•      Fatal (SAEs only)

Subjects who have moderate or severe on-going adverse events that are not unithiol linked will be referred to an appropriate government hospital/health facility on completion of the study and will be advised to consult a physician if the event is not considered to be related to the study drug. If it is related to the study drug, a follow-up visit will be arranged to manage the problem and to determine the severity and duration of the event. If appropriate, specialist review using government services will be arranged.

### Documenting AEs

Solicited and unsolicited AEs will be recorded on the participant’s CRF. The diagnosis, date and time of onset, outcome, severity, and relationship to dosing will be established. Details of any treatment or concomitant interventions will be recorded.

These will be recorded from the time of written informed consent until 6 months post cessation of trial treatment.

The following information will be collected:

•      Full details in medical terms and case description

•      Event duration (start and end dates, if applicable)

•      Action taken

•      Outcome

•      Seriousness criteria

•      Causality (i.e., relatedness to trial drug / investigation), in the opinion of the investigator

•      Whether the event would be considered expected or unexpected.

### Reporting serious adverse events (SAEs) and/or unexpected AEs

•      Every SAE occurring throughout the trial must be reported by telephone, e-mail, or fax to the sponsor (LSTM) and the DSMB within 48 hours, even if the investigator considers the SAE not related to the study drug. The investigator will then complete a hard copy SAE report as soon as possible and submit this to the sponsor, DSMB, SERU and PPB in accordance with their respective guidelines.

•      Any relevant information concerning the adverse event that becomes available after the SAE report form has been sent (outcome, precise description of medical history, results of the investigation, copy of hospitalisation report, etc.) will be forwarded to the sponsor, DSMB, SERU and PPB in a timely manner, the anonymity of the subjects shall be respected when forwarding this information.

•      The DSMB may ask for the study to be stopped, or for an extended study hold to be applied while further data and information are sought. The DSMB will make its recommendation to the Sponsor, who will have ultimate responsibility for acting on the recommendation.

•      Any study related SUSAR or serious adverse event related to participation in the study must be reported by telephone, e-mail, or fax to the sponsor (LSTM) and the DSMB within 48 hours. A hard copy SUSAR report will be completed as soon as possible and submitted to the sponsor, DSMB, SERU and PPB in accordance with their respective guidelines.

•      The SUSAR and SAE reports will be submitted to PPB through the online system at
www.pv.pharmacyboardkenya.org. The sponsor pledges to inform the authorities of any trial discontinuation and specify the reason for discontinuation. 

## Emergency procedures

### Equipment and drugs

The inpatient facility will be stocked with the appropriate equipment and drugs to manage emergencies that may arise whilst testing an IMP. This will include giving sets, intravenous fluids, oxygen, ventilation equipment and adrenaline.

### Follow-up of participants

Every reasonable effort will be made to follow-up subjects who have adverse events. Any subject who has an ongoing adverse event at the follow-up visit will be followed up, if possible, until resolution.

### Notification of deaths

All deaths will be reported to the sponsor, SERU, and PPB, irrespective of whether the death is related to disease progression, the IMP, or an unrelated event.

### Pregnancy

All pregnancies within the study period (either the subject or the subject’s partner) will be reported to the Principal Investigator and Sponsor within 24 hours of notification. The pregnancy will be followed to term at minimum, and the baby will be examined at 6 weeks after delivery (with further reviews to be arranged at the discretion of the responsible paediatrician).

### Procedures for reporting any protocol violation(s)

If any changes to the study are necessary during the study a formal amendment will be presented to the sponsor prior to submission to the relevant ethical and regulatory agencies for approval unless to eliminate an immediate hazard(s) to study participant without prior ethics approval. Any unforeseen and unavoidable deviations from the protocol will be documented and filed as a protocol non-compliance in the Trial Master File, with explanation.

## Statistics

The statistical analysis plan has been uploaded to the
Harvard Dataverse
^
41
^. The study is not powered to detect statistically significant differences between groups, although a cut-off p-value ≤0.05 will be applied to any comparisons.

### Pharmacokinetics

Pharmacokinetic outputs will include drug concentrations at each dose level during the first 24-hours and at each follow-up visit. Except for preliminary data to guide multiple dosing regimens that avoid accumulation, pharmacokinetic analysis will be completed after all participants have been dosed. Pharmacokinetic analysis will be undertaken at the University of Liverpool, UK. Area under the curve will be calculated from the plasma drug concentration time curve during the initial 24-hours. The maximal concentration (Cmax), time to maximum concentration (Tmax) and the half-life (t1/2) will be calculated.

### Pharmacodynamics

Pharmacodynamic outputs will vary between assay and are exploratory. For the fluorogenic substrate assay the area under the fluorescence-time curve will be compared between dosing groups using ANOVA and an appropriate post-hoc test (e.g., Tukey’s). The time to plateau and time to mid-point of fluorescence (Km) of the fluorescence-time curves will also be compared with this approach. These same measures will be calculated for the plasma clotting assay. Further assays will be developed, and analysis will be planned as appropriate.

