## Abstract

**Background:** Snakebites affect over 5 million people each year, and over 100,000 per year die as a result. The only available treatment is antivenom, which has many shortcomings including high cost, intravenous administration, and high risk of adverse events. One of the most abundant and harmful components of viper venoms are the zinc-dependent snake venom metalloproteinases (SVMPs). Unithiol is a chelating agent which is routinely used to treat heavy metal poisoning.
*In vivo* experiments in small animal models have demonstrated that unithiol can prevent local tissue damage and death caused by a certain viper species. This phase I clinical trial will assess the safety of ascending doses of unithiol with a view for repurposing for snakebite indication.

**Methods:** This open label, single agent, phase I clinical trial of a repurposed drug has a primary objective to evaluate the safety of escalating doses of unithiol, and a secondary objective to describe its pharmacokinetics. In total, 64 healthy Kenyan volunteers from Kilifi County will be dosed in consecutive groups of eight, with dose escalation decisions dependent on review of safety data by an independent data safety monitoring board. Four groups will receive ascending single oral doses, two will receive multiple oral doses, and two will receive single intravenous doses. Follow-up will be for 6-months and includes full adverse event reporting. Pharmacokinetic analysis will define the Cmax, Tmax, half-life and renal elimination.

**Conclusions:** This clinical trial will assess the safety and tolerability of a promising oral therapeutic in a relevant setting where snakebites are prevalent. Unithiol is likely to be safer than antivenom, is easier to manufacture, has activity against diverse snake species, and can be administered orally, and thus shows promise for repurposing for tropical snakebite.

**Pan African Clinical Trials Registry:** PACTR202103718625048 (3/3/2021)

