## Sample size determination

As this is a phase I clinical trial, with a primary aim to evaluate the safety of the escalating unithiol doses, a sample size calculation has not been conducted. Participants will be dosed in groups of eight, which is a commonly used design in phase I clinical trials
^
41
^.

The number of cohorts will be guided by the safety and tolerability of unithiol. Additional cohorts may be added if adverse events occur that, following review by the DSMB, warrant smaller increments in dose escalation or expansion at a dose level.

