## Randomisation procedure

Subjects will be allocated to a dosing cohort using stratified permuted block randomization. Stratification will be according to sex and age. Following the screening visit (and prior to attendance at the in-patient facility), participants will be asked to attend to receive the results of the clinical investigations, to be informed of their eligibility and to be informed of their allocation following randomization. Throughout the study, a minimum of four participants (randomly selected) will be on stand-by for each dosing cohort – to replace any participants that cannot be dosed. There is no placebo group and therefore this is not a randomized controlled trial. Participants in dosing cohorts that involve sentinel dosing will undergo a second step of randomization, to allocate individuals for sentinel dosing. The study team member responsible for randomizing subjects will be blinded to the subject’s identity and any information related to the subject except for their sex and age. Once randomization is complete, cohort allocation will be unconcealed. The study team and the participants will not be blinded.

Enrolment into the trial will begin the night before dosing. The participant will be reviewed by a study team member in the in-patient facility. Any concerns or questions the participant may have will be answered. Any participants that do not arrive or cannot be dosed due to becoming ineligible (e.g., due to illness) will be replaced, as detailed below.

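### Cohorts are stratified by sex and age, but the stated pharmacodynamic ANOVA names neither factor; if either predicts the assay, the test is conservative and loses power

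*Protocol article*

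**What the plan says.** On allocation, the Randomisation procedure section of the protocol article states: "Subjects will be allocated to a dosing cohort using stratified permuted block randomization. Stratification will be according to sex and age". The Recruitment section says the same and plans a cap for each sex. The Study population section aims for equal numbers of men and women in each cohort.

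On analysis, the Pharmacodynamics paragraph under Statistics says that, for the fluorogenic substrate assay, "the area under the fluorescence-time curve will be compared between dosing groups using ANOVA and an appropriate post-hoc test". Tukey's test is given as an example. The time to plateau and time to mid-point are handled in the same way, and the same measures are calculated for the plasma clotting assay. Dosing group is the only factor named. The opening of the Statistics section adds that "a cut-off p-value ≤0.05 will be applied to any comparisons".

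On status, the same text says: "Pharmacodynamic outputs will vary between assay and are exploratory". The Statistics section says: "The study is not powered to detect statistically significant differences between groups". Under Sample size determination, "a sample size calculation has not been conducted". The design is described in the Abstract: "64 healthy Kenyan volunteers from Kilifi County will be dosed in consecutive groups of eight".

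**The concern.** Stratified allocation makes the cohorts alike in sex and age. If either factor affects the assay result, the comparison between cohorts is largely free of that effect. An ANOVA on dosing group alone still counts the effect as unexplained variation within cohorts. The F test and the post-hoc contrasts then use an error term larger than the one that governs the comparison. The test rejects less often than its nominal 5% when there is no difference, and it misses more real differences.

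What is at stake is precision in an exploratory comparison with eight people per cohort. The section justifying the doses, and the Pharmacodynamics section under the assessment heading, both allow pharmacodynamic data from the single dosing stage to inform the multiple-dose regimen if the assay proves reliable. It is therefore reasonable not to give precision away.

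**Working it through.** The article states no power, effect size or standard deviation for this comparison, so there is no figure of its own to reproduce. The check asks how far an ANOVA on dosing group alone departs from its nominal behaviour.

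**Inputs from the protocol article**
- Cohort size n = 8 (Dose section, Table 2).
- Number of cohorts compared G = 4, the single ascending oral cohorts, so N = 32. With all eight cohorts, N = 64.
- Significance level 0.05 (Statistics).
- Stratification factors: sex and age. Age bands and block size are not given.

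**Assumptions not in the article**
- Two age bands, with the four sex-by-age cells exactly balanced in each cohort.
- Additive sex and age effects of equal size, and normal errors.
- R², the share of within-cohort variance explained by sex and age, varied from 0 to 30%.
- For power, a linear trend across the four cohorts with a range of 1.75 SD from lowest to highest (1.9 SD for eight cohorts), in units of the SD within a sex-by-age cell.

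**Size of the error term**

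Set the variance within a cell to 1. The strata then add variance R²/(1 − R²). Under exact balance none of it reaches the between-cohort mean square, and all of it enters the residual, which has N − G degrees of freedom:

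E(MS error) = 1 + [R²/(1 − R²)] × N/(N − G)

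With N = 32 and G = 4, N/(N − G) = 32/28 = 1.143.
- R² = 10%: 1 + 0.111 × 1.143 = 1.127. Standard errors of contrasts are inflated by about √1.127 = 1.06.
- R² = 20%: 1 + 0.250 × 1.143 = 1.286. The inflation is about √1.286 = 1.13.
- R² = 0: 1.000, no inflation.

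**Simulation**

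Each scenario used 40,000 simulated trials. The Monte Carlo standard error is about √(0.05 × 0.95/40,000) = 0.1 percentage points for type I error and √(0.8 × 0.2/40,000) = 0.2 points for power. Results for four cohorts of eight:

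| R² of strata | Type I error, group only | Type I error, with sex and age | Power, group only | Power, with sex and age |
|---|---|---|---|---|
| 0% | 5.2% | 5.2% | 83.5% | 83.0% |
| 5% | 4.3% | 5.1% | 81.1% | 82.9% |
| 10% | 3.4% | 4.9% | 78.7% | 83.1% |
| 20% | 2.0% | 5.0% | 72.2% | 83.2% |
| 30% | 1.2% | 4.9% | 62.9% | 82.8% |

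With all eight cohorts the pattern is the same. At R² = 10%, type I error is 2.8% and power 92% against 95%. At 20%, they are 1.4% and 87% against 95%. These figures deserve less weight, because the eight cohorts may not come from one randomised pool.

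**Cost of adjusting**

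Residual degrees of freedom fall from 32 − 4 = 28 to 32 − 4 − 2 = 26. When the strata explain nothing, power falls from 83.5% to 83.0%, a loss of 0.5 points.

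**The case against.** The strongest objection is that this is a condensed article with a separate statistical analysis plan that is not shown. The word ANOVA does not exclude further factors, and model terms are commonly left to the plan. This stands in part: the article is silent on sex and age rather than ruling them out. It does, however, go beyond deferring to the plan. It names the test and the grouping factor, and as worded the method does not use the factors by which the trial allocates.

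The second objection is that the effect depends on sex or age predicting the assay. This stands in full. A reader might infer that the error term is simply too large and that the 5% cut-off does not hold, but no figure in the article supports an unconditional statement. Nor does the weight range of 50 to 120 kg at fixed oral doses show that sex is prognostic. Weight is not a stratification factor, no weights by sex are given, and the intravenous cohorts are dosed per kilogram.

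Third, balance is sought rather than guaranteed. Equal sex numbers are an aim, stand-by participants replace non-attenders, and screening is expected separately for the single and multiple dosing stages. This also stands. With imperfect balance some stratum variance reaches the between-cohort comparison, so the size of the test would lie closer to 5% than in the table.

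Fourth, a reader might infer that the choice of multiple-dose regimen is compromised. The article does not tie that choice to a significant difference between cohorts. For the first multiple-dose cohort it looks for the smallest dose with adequate inhibition, and only if the assay is judged reliable. It also says that escalation does not depend on this assay.

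**Conclusion.** The point holds in conditional form. The article stratifies allocation by sex and age and then states a pharmacodynamic comparison that names neither. If one or both predict the assay result, the stated test is conservative. For four cohorts of eight the power loss is about 4 points when the strata explain 10% of within-cohort variance (79% against 83%) and about 11 points when they explain 20% (72% against 83%). At 5% it is under 2 points. At zero there is nothing to correct. These figures rest on assumed values of R², an assumed trend of 1.75 SD, two age bands and exact balance.

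Severity is low. The outcome is exploratory, the article disclaims power for between-group differences, and the error runs towards missed differences rather than false claims. A reader might extend the point to pharmacokinetic parameters or laboratory changes. The article states no between-cohort test for either; those results are to be calculated or described, so the point is confined to the pharmacodynamic measures.

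**What to change.** In the Pharmacodynamics paragraph under Statistics, or in the statistical analysis plan if it does not already do so, state that these measures are compared with a linear model containing dosing group, sex and age (age in the bands used for stratification, or in years). Take the post-hoc contrasts from that model. Apply it primarily to cohorts randomised within the same stage, and describe any comparison between the single and multiple dosing stages as not necessarily randomised.

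The change is one sentence. Sex and age are already collected. It costs about two residual degrees of freedom, or about half a point of power if neither factor matters.

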### Dose

Participants will be dosed in cohorts of 8. Cohorts for single oral doses are abbreviated as ‘C’, single intravenous dose cohorts as ‘CIV’ and multiple oral dosing cohorts as ‘CM.’ There will be four single ascending oral dosing cohorts (C1-C4), two intravenous dosing cohorts (CIV1 and CIV2) and two multiple dosing cohorts (CM1 and CM2). The anticipated dose escalations are summarised in
Table 2. The dosing regimen in
Table 2 represents the anticipated dose escalations that will be followed should the DSMB have no safety concerns. The highest single oral dose of unithiol that will be administered is 1,500 mg. Any increase above 1,500 mg would require approval from the Sponsor and the ethics and regulatory committees. Following review by the DSMB, dose levels may be repeated, smaller increments in dose escalation may be adopted or dose levels may be lower than the preceding dose level and, therefore, additional cohorts may be included. The DSMB will make these decisions based on adverse event data.

**Table 2. T2:** Summary of dosing regimens.

Single dosing *(and CIV1)*		
Cohort name	Number of subjects	Dose
C1	8	300 mg oral
C2	8	900 mg oral
C3	8	1200 mg oral
C4	8	1500mg oral
CIV1	8	3 mg/kg intravenous single dose
Multiple dosing *(and CIV2)*		
CM1	8	300–1200 mg oral qds for 2 to 3 days
CM2	8	1500 mg oral (or highest tolerated dose from single dosing) qds for 2 to 3 days
CIV2	8	Depends on emerging data (5–10 mg/kg intravenous) single dose

Additional dosing cohorts may be added depending on emerging safety data. Eight cohorts and the above dose escalations represent the maximum dose increases that would occur assuming reassuring safety data.

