### Justification for the proposed dose, route of administration, dosage regimen and treatment period

The starting dose for the oral single ascending dose stage will be 300 mg. This is a routine dose recommended for the treatment of heavy metal poisoning
^
38,
39
^. The maximum dose that will be administered during the oral single ascending dose stage will be 1,500 mg. This dose has been selected based on pre-clinical in-vitro assays that have shown that high concentrations of unithiol are required to inhibit the pro-coagulant effects of snake venom
^
21
^. In this experiment, 150 µM of unithiol was required to prevent consumption coagulopathy. Given that previous in-human pharmacokinetic analysis has identified a C
_max_ of 25 µM following administration of 300 mg oral
^
33
^, it has been estimated that a dose of 1,500 mg would be required to achieve a peak plasma concentration sufficient to inhibit coagulopathy. Published reports of dose levels of unithiol equivalent or higher than 1,500 mg oral suggest that this dose is safe
^
24,
31,
32
^.

The dose that will be given to the first intravenous dosing cohort (CIV1) will be 3 mg/kg. This has been selected as it is at the lower range of the routinely recommended dose for acute heavy metal poisoning (3–5 mg/kg)
^
27,
40
^. Previous pharmacokinetic analyses have shown that 3 mg/kg intravenous achieves an initial plasma concentration of 100 µM
^
27
^. At least one further intravenous dosing cohort will be included. The dose administered will be decided by the DSMB based on emerging data from the first stage of the trial. This dose is expected to be 5 mg/kg, although a dose of up to 10 mg/kg may be selected, depending on emerging safety and pharmacodynamic data.

For the multiple dosing cohorts (CM1 and CM2), the study team will select doses that show the optimum profile for treating snakebite, based on safety, tolerability and any available pharmacokinetic and pharmacodynamic data. If the pharmacodynamic data shows a dose response relationship and is deemed to demonstrate sufficient reliability, the investigators will aim to select CM1 based on a minimum dose associated with adequate

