### Pharmacodynamics

An exploratory outcome is to assess the efficacy of unithiol to inhibit the pathogenic actions of venom,
*ex vivo*. If the pharmacodynamic assay produces results that are deemed reliable, then pharmacodynamic data from the single dosing stage could be used to guide the dosing regimen for the multiple dosing stage. If the pharmacodynamic assay does not produce useful results, then dose and dosing frequency decisions will be made based on safety and preliminary pharmacokinetic data.

*Ex vivo* assays will be developed for the purposes of establishing a dose-response and estimating a pharmacodynamic profile. These assays will rely on spiking subjects’ plasma with venom
*ex vivo* and measuring activity of snake venom metalloproteinases. These assays are being developed for the purposes of this study, and a published validated assay does not exist. It would not be appropriate to assign these assays as primary outcome variables as they are experimental and represent an indirect estimate of efficacy.

These assays will continue to be refined during this study. They primarily represent a tool to compare venom metalloproteinase inhibition between subjects receiving different doses of unithiol, rather than a direct measure of efficacy. Where possible, these assays will be conducted and refined in the laboratory facilities at KEMRI-CGMRC. Split samples will also be shipped to Liverpool School of Tropical Medicine Centre for Snakebite Research & Interventions (LSTM CSRI).

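### The exploratory PD measures are compared between dose groups only by a test that ignores dose order, although a dose-response is one stated purpose of the assays and may guide the CM1 dose

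*Protocol article*

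**What the plan says.** - **Test.** Protocol article, Statistics, Pharmacodynamics: the area under the fluorescence-time curve "will be compared between dosing groups using ANOVA and an appropriate post-hoc test", with Tukey's test as the example. Time to plateau and time to mid-point are compared in the same way, and the same measures are calculated for the plasma clotting assay. No trend test, ordered contrast or dose-response model is named. The outputs are called exploratory.
- **Purpose.** Assessment of pharmacokinetics and pharmacodynamics, Pharmacodynamics: the "assays will be developed for the purposes of establishing a dose-response and estimating a pharmacodynamic profile". The same section adds: "They primarily represent a tool to compare venom metalloproteinase inhibition between subjects receiving different doses of unithiol".
- **Use.** Justification for the proposed dose: "If the pharmacodynamic data shows a dose response relationship" and is judged reliable enough, the investigators aim to select CM1 from the minimum dose with adequate ex vivo inhibition.
- **Significance rule.** Statistics: "The study is not powered to detect statistically significant differences between groups", although "a cut-off p-value ≤0.05 will be applied to any comparisons".
- **Size.** Dose: "Participants will be dosed in cohorts of 8". The four single oral cohorts C1-C4 receive 300, 900, 1,200 and 1,500 mg.

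**The concern.** The section on the assays sets two aims: to establish a dose-response, and to compare inhibition between doses. The analysis section serves only the second. If the labels 300, 900, 1,200 and 1,500 mg were shuffled among the four cohorts, the ANOVA F statistic and p-value would not change. The test therefore cannot by itself say whether inhibition rises with dose, and Tukey's pairs give no slope.

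This is more than detail left to the SAP, because the article names a method and that method covers only one of its two aims. At stake is the quality of the evidence on a dose-response that may inform the CM1 dose. If inhibition rises in graded steps, the planned test is less likely to detect it than one that uses the order. With 8 per cohort, a p-value cut-off alone also invites reading a non-significant result as no difference.

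**Working it through.** The protocol gives no PD effect size, SD, curve shape or power, so there is no stated figure to reproduce. The check compares two tests on the same assumed data.

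**From the protocol:** n = 8 per cohort; k = 4 ordered single oral cohorts (300, 900, 1,200, 1,500 mg); α = 0.05, with sidedness not stated and taken as two-sided.

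**Assumed:** normal data with equal SD (σ = 1); one value per participant; a difference D between 300 and 1,500 mg of 0.5 to 2.0 SD; the curve shape.

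**ANOVA.** Noncentral F with 3 and 28 df, critical value 2.947, noncentrality λ = n Σ(μᵢ − μ̄)².

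**Trend on log dose.** Noncentral t with 28 df, critical value 2.048, noncentrality δ = √n Σcᵢμᵢ / √Σcᵢ², where cᵢ is ln(dose) minus its mean: −1.024, 0.075, 0.363, 0.586.

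**Worked case, log-linear response, D = 1.25.**
1. On a 0-to-1 scale the cohort means are 0, 0.683, 0.861 and 1, with Σ(μᵢ − μ̄)² = 0.590.
2. λ = 8 × 0.590 × 1.25² = 7.37, so ANOVA power is 55%.
3. The contrast matches the curve, so δ = √7.37 = 2.72 and trend power is 75%.

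**Log-linear response over a range of D:**

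| D (SD) | ANOVA | Log-dose trend | Difference (points) |
|---|---|---|---|
| 0.5 | 12% | 18% | +6 |
| 1.0 | 37% | 55% | +19 |
| 1.25 | 55% | 75% | +20 |
| 1.5 | 72% | 88% | +16 |
| 2.0 | 94% | 99% | +5 |

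(Differences are taken before rounding.)

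**Other shapes at D = 1.25, same log-dose contrast:**

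| Shape | ANOVA | Log-dose trend |
|---|---|---|
| Linear in dose | 51% | 70% |
| Emax, ED50 500 mg | 56% | 75% |
| Flat from 900 mg | 66% | 81% |
| Only 1,500 mg works | 66% | 37% |

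In the last row, Σ(μᵢ − μ̄)² = 0.75, so λ = 8 × 0.75 × 1.25² = 9.38, but δ is only √8 × 0.586 × 1.25 / √1.528 = 1.68. At D = 1.5 the same shape gives 83% for ANOVA and 49% for the trend.

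**Pairwise tests.** Among four cohorts, Tukey's test calls a pair significant only if the observed difference exceeds q/√n = 3.861/√8 = 1.37 SD. A non-significant pair is therefore weak evidence of no difference.

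**The case against.** The strongest case for the plan has four parts.

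1. **ANOVA serves a stated aim.** The protocol calls the assays primarily a tool to compare inhibition between doses. The CM1 choice looks for a minimum adequate dose, which a single slope does not identify. This stands, and is a reason to keep the group comparison.
2. **A trend test can do worse.** The dose justification says 150 µM was needed to prevent coagulopathy, quotes a Cmax of 25 µM after 300 mg, and estimates that 1,500 mg is required. An effect mainly at the top dose is therefore plausible, at least for the clotting assay, and there the trend loses about 30 points. This also stands.
3. **PD is exploratory and no power is claimed.** The dose escalation schedule says that escalation does not depend on the PD assay. This limits the weight of the point but does not remove the mismatch.
4. **A separate SAP exists.** It may add a trend analysis. But the article itself fixes a method, and that method leaves one stated aim unaddressed.

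A reader might infer more than the documents support:
- *That ANOVA at p≤0.05 triggers the CM1 choice.* Nothing says so. The choice rests on safety, tolerability, and available PK and PD data, with the PD data first judged reliable.
- *That pooling all eight cohorts in one comparison would distort that choice.* CM1 and CM2 have not been dosed when the CM1 dose is selected, so such a comparison could not inform it.
- *That the cut-off would hide adverse-event differences.* The Safety analyses section plans description of adverse events and names no test between cohorts.

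**Conclusion.** The point holds as a mismatch between one stated aim and the named analysis. ANOVA with a post-hoc test ignores dose order and gives no dose-response estimate, while the protocol wants a dose-response and may use it for CM1.

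For a log-linear response with 8 per cohort, the log-dose trend gains about 5 to 20 points of power over D = 0.5 to 2.0 SD, with the peak near 1.25 SD. It would be tempting to say that the plan simply wastes 20 points. That is not supported: 20 is close to a best case, it depends on an effect size and curve shape that the protocol does not give, and the sign reverses (37% v 66% at 1.25 SD) if only the top dose works. Neither test is better for every shape, so the two belong together. The consequence is modest.

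**What to change.** In Statistics, Pharmacodynamics, and in the SAP if it does not already say so:

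- For C1-C4, add a prespecified ordered dose-response analysis: a trend on log dose, or a regression on the measured unithiol concentration. Use the participant as the unit of analysis and report the slope with its 95% CI.
- Keep ANOVA and Tukey's test alongside it, not demoted, to cover a threshold or other non-graded response.
- Present the IV and multiple-dose cohorts separately, since route and regimen differ from C1-C4.
- Report PD comparisons as estimates with 95% CIs rather than by p≤0.05 alone.

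The cost is wording, with no extra participants or samples. The trend's weakness when only the top dose works should be stated, so that a null slope is not read as no effect.
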